### Data Collection

2.5

Throughout all the sessions, trial conduct will be monitored continuously by the study investigators. Monitoring procedures will include verification of protocol adherence, completeness of data collection, and reporting of adverse events at each study session. Given the small sample size, short duration, and minimal‐risk nature of the study, no independent or external trial monitoring is planned.

For each participant, demographic and clinical data will be collected together with scores from the administered questionnaires. Physiological signals will be acquired using the EmbracePlus wearable device, including PPG, which records variations in blood volume associated with each heartbeat, enabling estimation of heart rate and analysis of HRV; EDA, which reflects sympathetic activation through eccrine sweat gland activity and serves as an indicator of physiological arousal, with pain‐related parameters extractable from the raw signal as well as from its tonic (slow changes) and phasic (rapid changes) components [8]; skin temperature (SKT), providing an indirect measure of sympathetic nervous system activity primarily influenced by peripheral blood flow; and acceleration, capturing physical activity and movement‐related data.

These signals will be analyzed to quantify stress levels, physical and mental workload associated with VR use, and potential side effects during task execution. In addition, accelerometric data from the mTest3 system will be collected to capture lower limb and trunk motion, allowing the derivation of objective gait parameters and the characterization of gait across sessions. Video recordings of gait tests will be processed through markerless skeleton‐based motion analysis to extract spatiotemporal gait features. This approach will be tested through a comparison with wearable sensors, given its reduced impact on natural gait [45]. Both physiological and motion‐related data will be considered alongside questionnaire outcomes to examine patterns in user experience and gait characteristics.

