### Endpoints and Statistical Analysis

2.6

The feasibility sample size of 12 participants with MS was chosen to provide a sufficient dataset to analyze the practicality of implementing a VR‐based intervention combined with a passive orthosis. Accounting for an estimated 20% dropout, the sample size is consistent with methodological recommendations for feasibility studies [46].

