#### Secondary Endpoints

2.6.2

Descriptive changes and trends in gait and balance parameters across sessions (T1, T2, and follow‐up T3), based on spatiotemporal parameters and clinical test results (2MWT, T25FWT, TUG).Associations between physiological signals, wearable/video‐based kinematic data, and subjective clinical or workload scores.Feasibility of establishing preliminary, proof‐of‐concept ML pipelines for gait [47, 48, 49] and physiological data, focusing on technical performance, data quality, and evaluating pipeline viability to inform future predictive models in adequately powered studies.

Continuous data (e.g., gait parameters, questionnaire scores) will be summarized using descriptive statistics (means, medians, standard deviations). Comparisons between sessions (T1–T2 and T1–T2–T3) will be conducted using paired or nonparametric tests to examine trends and variability in the data. Correlations between clinical scores and sensor/video‐based measures will be determined with Pearson or Spearman coefficients. Associations between physiological signals and subjective workload/motion sickness (NASA‐TLX, IPQ, and SSQ) will also be investigated through correlation analyses. The feasibility of establishing preliminary ML pipelines (e.g., using simpler algorithms like regularized linear models or support vector machines) to explore associations with gait quality and participant well‐being from inertial and physiological data will be evaluated. Although the study includes only 12 participants, each participant is expected to contribute multiple gait trials, with each gait cycle constituting an individual analysis instance for feature extraction and model input. Because these instances are not statistically independent, model evaluation will be performed leave‐one‐subject‐out cross‐validation (LOSO‐CV), ensuring that all gait cycles from a given participant are held out together during testing to prevent data leakage, mitigate potential model overfitting and overly optimistic performance estimates. Given the pilot nature of the study, all ML analyses will remain strictly exploratory and results will be reported using descriptive performance metrics (e.g., balanced accuracy, F1‐score) to demonstrate pipeline feasibility rather than model generalizability.

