Beyond technical limitations, successful translation of VR and sensor‐based evaluations into routine clinical workflows requires careful consideration of the operational burden placed on both patients and clinical sites, as highlighted in recent frameworks for digital health technology deployment [55]. For patients, the simultaneous use of multiple wearables and VR headsets can induce physical or cognitive fatigue, particularly in individuals with MS who already experience disease‐related exhaustion. In our protocol, this is mitigated through short‐duration test protocols, structured rest intervals, and the availability of mixed‐reality modes to minimize cybersickness. For study sites and clinical staff, barriers include the time needed for multi‐device setup, sensor calibration, software management, and raw data integration. To minimize site burden and support scalability, future iterations of the VIRTUE framework will prioritize streamlining the sensor kit, such as evaluating whether video‐based markerless tracking can replace shoe‐worn IMUs and developing automated software pipelines to simplify data synchronization and reporting for clinicians. This user‐centered perspective will also extend to home‐based assessments, aiming to simplify setup requirements and minimize participant burden during ecological monitoring of daily activities. Ultimately, the present study is crucial for gathering direct feedback from both patients and clinicians about the usability and feasibility of the proposed instrumentation, laying the groundwork for optimizing the framework prior to its deployment in larger cohort studies.

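### Ordinary Pearson/Spearman correlation is planned for an association endpoint whose measures are repeated up to about 10 times in each of 12 participants, with no unit of analysis and no allowance for dependence

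*Protocol article*

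**What the plan says.** The second secondary endpoint in section 2.6.2 is the association between physiological signals, wearable or video kinematics, and clinical or workload scores. Two sentences give its analysis. Correlations between clinical scores and sensor or video "measures will be determined with Pearson or Spearman coefficients". Associations of physiological signals with NASA-TLX, IPQ and SSQ "will also be investigated through correlation analyses". Neither sentence says whether a participant contributes one value or several.

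Later in the same section, individual gait cycles are the inputs to the machine-learning models. There the text reads "Because these instances are not statistically independent" and adopts leave-one-subject-out cross-validation. The Discussion repeats this point, again only for machine learning. The correlations have no counterpart.

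Section 2.4 sets the data structure. At T1 each participant does the T25FWT and TUG under four conditions (VR on or off, ExoBand on or off), with physiological and gait recording during each test and NASA-TLX around the VR and brace conditions. T2 repeats T1, and T3 repeats it without VR. SSQ, IPQ, MFIS, BBS and MSWS-12 are collected by session, not by condition.

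**The concern.** A plain Pearson or Spearman coefficient, with its usual interval or test, assumes that each pair of values comes from a different, independent unit. Here the natural dataset for NASA-TLX against physiology or gait has many rows per person. NASA-TLX is collected around conditions in order to show differences between them, so one row per condition is a realistic reading of the plan.

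Pooling those rows does two kinds of harm. The first is to the estimate. A pooled coefficient blends two questions: whether people with higher workload scores have higher arousal (between persons), and whether arousal rises in the condition where a given person reports more workload (within person). The two can differ in size and even in sign. Calling the analysis exploratory does not make the blend interpretable. The second is to precision. 12 people with 8 to 10 rows each are treated as 96 to 120 independent observations, so chance associations look well established.

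What is at stake is one secondary endpoint and the leads it passes to a later trial. The primary feasibility endpoint is not affected.

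**Working it through.** **Is there a figure to reproduce?** No. Section 2.6 gives 12 participants with an estimated 20% dropout, and no precision target for correlations. Expected completers are 12 × 0.8 = 9.6.

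**Records per participant (section 2.4).**
- By condition: 4 (T1) + 4 (T2) + 2 (T3, no VR) = 10 per test at most, or 8 over T1 and T2. The exact NASA-TLX count depends on how its before-and-after schedule is read.
- By session: about 2 to 3 for SSQ, IPQ, MFIS, BBS and MSWS-12.
- Pooled rows: 12 × 3 = 36, 12 × 8 = 96, 12 × 10 = 120.

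**Assumptions.** The article gives no intraclass correlation (ICC), so 0.3, 0.5 and 0.7 are assumed, equal in both variables. A two-sided 5% test is used as the yardstick; the article states none.

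**Approximation.** With m records per person and no true association, the variance of the pooled r is inflated by about 1 + (m − 1) × ICC². For m = 8 and ICC = 0.5 this is 1 + 7 × 0.25 = 2.75. The true standard error is then √2.75 = 1.66 times the naive one, and the rejection rate is 2 × [1 − Φ(1.96/1.66)], or about 24%.

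**Simulation.** 12 participants, true correlation 0, 10,000 runs, plain Pearson test on pooled rows:

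| Records per person | ICC 0.3 | ICC 0.5 | ICC 0.7 |
|---|---|---|---|
| 1 | 4.6% | 5.4% | 5.1% |
| 3 | 6.7% | 10.7% | 16.7% |
| 8 | 12.5% | 22.9% | 37.0% |
| 10 | 13.7% | 27.4% | 40.4% |

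Repeat simulations agree to within about one percentage point. Repeated-measures correlation stays at about 5% under the same conditions.

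**Interval for an observed r = 0.5 (Fisher z).** atanh(0.5) = 0.549 and SE = 1/√(n − 3).
- n = 12: SE = 1/√9 = 0.333; 0.549 ± 1.96 × 0.333 gives -0.104 to 1.203; back-transformed, **-0.10 to 0.83**.
- n = 10, after dropout: -0.19 to 0.86.
- 36 pooled rows treated as independent: 0.21 to 0.71.
- 96 pooled rows: 0.33 to 0.64.
- 120 pooled rows: 0.35 to 0.62.

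So the same observed coefficient is compatible with no association at n = 12, and looks firmly positive once rows are pooled.

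**The case against.** The strongest reply is that pooling is nowhere stated. One value per participant, or a separate coefficient for each condition and session with n = 12, would make Pearson or Spearman valid, and the table's first row confirms about 5%. The article states no p-values, alpha or intervals for the correlations. Section 2.2 says that these measures will be interpreted descriptively and exploratorily. Most of the scales give only two or three values per person, where inflation is modest. A condensed article may also leave the unit of analysis to a fuller document.

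Much of this stands. The narrowing is conditional on pooling, its size depends on an ICC that the article does not give, and the larger rates apply only to measures taken by condition. But the method itself is named, and either use of it is poor for these data: pooling ignores dependence, while one value per person discards the within-person contrast that the four-condition design was built to provide. The authors acknowledge dependence among the same participants' repeated observations and act on it only for machine learning.

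A reader might infer two stronger points that the article does not support.
- *Correlation is the only tool for sensor measures.* It is not. Section 2.6.2 also lists descriptive statistics, paired or nonparametric between-session tests, and machine-learning pipelines.
- *The study will use correlation to decide whether video can stand in for sensors.* Section 2.5 says of video analysis that "This approach will be tested through a comparison with wearable sensors", but no method is named there or in the Discussion. The sentence quoted in section 2.6.2 concerns clinical scores against sensor or video measures, not video against sensor. The Discussion's phrase "markerless tracking can replace" belongs to a sentence about future iterations of the framework. A missing agreement statistic is a detail that an article may omit.

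**Conclusion.** The point holds in a limited form. The protocol names an ordinary coefficient for a secondary endpoint whose data are partly repeated up to about 10 times per person. It sets no unit of analysis and handles dependence only for machine learning. If records are pooled, a nominal 5% test has a true level of about 12% to 37% with 8 records and about 7% to 17% with 3, over an assumed ICC of 0.3 to 0.7, and the coefficient has no clear meaning. If one value per participant is used, the error rate is correct but the estimate is very imprecise. The article does not show which will be done, so it cannot be said that its intervals will be too narrow, only that nothing in the text prevents it. This is a should-fix item on an exploratory secondary endpoint, not a threat to the primary objective.

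**What to change.** In section 2.6.2, state the unit of analysis for each pair of measures.

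- **Measures repeated by condition** (NASA-TLX, physiological signals, gait parameters), and trends across sessions where within-person change is of interest: replace plain Pearson/Spearman with repeated-measures correlation, or with a mixed model with a participant random intercept. In the mixed model, enter the participant's mean and the deviation from it as separate terms, so that between-person and within-person associations are not blended again.
- **Scores taken once per person or once per session:** use one value per participant, from a session named in advance, and report r with its 95% CI.

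The cost is a few sentences and some extra analysis code on data already being collected. The price in results is wider, less favourable intervals. Section 3.1 reports recruitment as ongoing, so this can be settled before analysis.

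As a suggestion only: when the video-against-sensor comparison is reported, give bias and limits of agreement for each gait parameter, allowing for repeated pairs.

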### Study Objectives

2.2

The primary objective of this study is to investigate the feasibility of a monitoring system designed to test gait performance with a passive walking brace in VR environments that closely reproduce real‐life conditions, specifically assessing the framework's usability and overall acceptability. The system integrates wearable inertial sensors with routinely used functional clinical scales with the goal of determining whether this technological approach can provide clinicians with additional objective information, particularly regarding patients' adaptation to the orthosis and trends in gait parameters.

The secondary objectives include assessing the role of VR in replicating everyday contexts, such as the home, workplace, and public spaces, and examining its potential to enhance adaptation to assistive devices in daily life. The study also aimed to examine user satisfaction and technology acceptance in people with MS through validated questionnaires. Furthermore, we will analyze the feasibility of repeated longitudinal assessments and preliminary trends in gait and balance outcomes over time through a follow‐up session carried out 2 months after the last usage of the proposed system. Another objective is to understand the feasibility of characterizing orthosis‐assisted gait in individuals with MS using data collected from wearable inertial sensors and from video recordings processed through skeletal motion models during ambulatory sessions. Finally, the study will determine the technical feasibility of establishing preliminary, proof‐of‐concept ML pipelines. These exploratory analyses are strictly aimed at evaluating data quality, feature extraction workflows, and pipeline viability, rather than developing generalizable predictive models.

This study is designed as an interventional feasibility study and is not powered to detect clinical efficacy outcomes. Clinical, gait, and physiological measures will therefore be interpreted descriptively and exploratorily.

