### Data Management

2.7

The PI will act as data controller. Each participant will be assigned a pseudonymization code. Paper‐based records (i.e., patient record forms) will be stored at the UOSI‐RSM, IRCCS ISNB, and will be the only documents containing identifiable information. The master file linking pseudonymization codes with personal data will be securely retained by the PI.

For each participant:
Questionnaires and scale data from clinical sessions will be entered directly into REDCap (electronic data capture system) and recorded in the electronic CRF.Home‐based data will be collected via Microsoft Forms, pseudonymized prior to storage, and then archived in REDCap and the CRF.Physiological, spatiotemporal, and VIRTUE4ms‐extracted data will be pseudonymized and analyzed with dedicated in‐home programming codes.

All data will be handled in compliance with the General Data Protection Regulation (GDPR) and retained for 10 years. Pseudonymized datasets will be stored in password‐protected systems (i.e., online platforms such as REDCap or protected servers) accessible only to authorized research staff. Data analysis will be performed using statistical software tools such as Stata SE 16.0 or MATLAB.

Missing data will be reported and described for each outcome measure. Given the exploratory nature and small sample size of this pilot study, no formal imputation procedures will be applied. Analyses will be conducted on available data only.

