Lastly, the small sample size of the study necessitates repeated testing across four experimental conditions (VR on/off and ExoBand on/off) to achieve meaningful results, instead of having two separate groups, one using VR and the other in the non‐VR condition. This procedure must be completed in a single session, as splitting it across 4 days (one for each condition) would create organizational challenges for participants, who may not be able to come to the hospital on four consecutive days, and would also lead to substantial time‐related costs for the hospital staff. To minimize fatigue‐related biases, rest breaks will be provided. Future studies with larger cohorts will allow for more robust statistical analyses and group comparisons. Additionally, the limited subject cohort poses an inherent risk of model overfitting when exploring ML pipelines. Although each participant contributes multiple gait repetitions, yielding numerous segmented gait cycles as individual analysis instances, these repeated observations are not statistically independent. In our protocol, the risk of overfitting and data leakage is constrained by utilizing LOSO‐CV, ensuring all gait cycles from a given participant are held out together during testing, alongside simple regularized models. Consequently, any preliminary ML performance metric must be interpreted strictly as an indicator of automated workflow feasibility rather than a generalizable predictive result.

In summary, this protocol investigates the feasibility of a novel, multidimensional approach to gait rehabilitation with assistive devices in people with MS. By combining VR, wearable sensors, and advanced data analysis, it offers a pathway to overcome the limitations of conventional clinical methods, moving toward more personalized, scalable, and clinically relevant strategies.

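### Balanced accuracy and F1 describe the classifier, not data quality or workflow viability, so they cannot carry the pipeline-feasibility reading that the protocol gives them

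*Protocol article*

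**What the plan says.** Section 2.2 (Study Objectives) describes the machine-learning analyses as "strictly aimed at evaluating data quality, feature extraction workflows, and pipeline viability, rather than developing generalizable predictive models". Section 2.6.2 (Secondary Endpoints) makes this the third secondary endpoint, "focusing on technical performance, data quality, and evaluating pipeline viability", so it adds technical performance to the list. Section 3.2 (Expected Outcomes) also names technical performance.

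On measurement, section 2.6.2 takes multiple gait trials per participant, "with each gait cycle constituting an individual analysis instance for feature extraction and model input". Models are evaluated by leave-one-subject-out cross-validation, and "results will be reported using descriptive performance metrics (e.g., balanced accuracy" and F1), the stated purpose being "to demonstrate pipeline feasibility rather than model generalizability".

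On interpretation, the limitations in the Discussion (section 4) say that "any preliminary ML performance metric must be interpreted strictly as an indicator of automated workflow feasibility rather than a generalizable predictive result".

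On missing data, section 2.7 (Data Management) says that missingness will be described for each outcome measure, that nothing will be imputed, and that "Analyses will be conducted on available data only".

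**The concern.** The endpoint has three parts, and the only kind of measure named for it fits one of them. Balanced accuracy and F1 on a held-out participant estimate how well a fitted model classifies cycles from a person it has not seen. That is a fair description of technical performance. It does not measure data quality or workflow viability, because a cycle that could not be synchronised, segmented or turned into features is in neither the numerator nor the denominator.

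The protocol does more than leave the measure open. It says that the metrics demonstrate pipeline feasibility, and it instructs the reader to take any such metric strictly as an indicator of workflow feasibility. Followed literally, this lets a pipeline that discards many cycles look feasible, and lets a sound pipeline look poor because twelve people show little predictive signal. The endpoint is meant to inform later, adequately powered studies, for which the rate of loss in processing is a main planning figure.

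**Working it through.** The documents give no target, threshold or expected value for accuracy, F1 or cycle yield, so there is no stated figure to reproduce. The check is of logic, with an illustration on assumed data.

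**Definitions**, with TP, FN, TN and FP counted over surviving cycles only:

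- Balanced accuracy = ½ × [TP/(TP + FN) + TN/(TN + FP)]
- F1 = 2TP/(2TP + FP + FN)
- Yield = usable cycles / attempted cycles

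The first two contain no count of attempted cycles. If cycles are lost at random, TP, FN, TN and FP all shrink in the same expected proportion and the ratios stay put. Only yield changes.

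**Inputs.** From the protocol: 12 participants, gait cycle as the instance, leave-one-subject-out evaluation, available data only. Assumed, because the article states no class label: two balanced classes and 200 attempted cycles per participant (12 × 200 = 2,400). One feature x = 1.5 × class + participant effect (SD 0.5) + noise with SD 0.4 + 1.6q, where q is uniform on 0 to 1. The classifier cuts at the midpoint of the training class means. 300 repetitions.

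**Results (mean over repetitions)**

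| Nominal share kept | Random loss: BA / F1 | Noisiest cycles lost: BA / F1 | Whole participants lost: BA / F1 |
|---|---|---|---|
| 95% | 0.732 / 0.732 | 0.736 / 0.735 | 0.732 / 0.731 (actual 92%, 11 of 12) |
| 75% | 0.730 / 0.730 | 0.755 / 0.755 | 0.731 / 0.731 |
| 50% | 0.731 / 0.731 | 0.789 / 0.789 | 0.728 / 0.728 |
| 25% | 0.731 / 0.730 | 0.827 / 0.827 | 0.721 / 0.720 |

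At 25% yield under random loss, about 600 of 2,400 cycles remain (0.25 × 2,400), yet balanced accuracy differs by 0.001 from its value at 95%.

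**Check by formula.** With the cut at its expected place, a cycle of noise level q is classified correctly with probability Φ(0.75/√(0.25 + (0.4 + 1.6q)²)). This gives 0.879 at q = 0, 0.787 at q = 0.25, 0.718 at q = 0.5 and 0.642 at q = 1.

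- All cycles, Simpson's rule over q from 0 to 1: (0.879 + 4 × 0.718 + 0.642)/6 = 0.732. Random loss does not change this average.
- Noisier half lost, q from 0 to 0.5: (0.879 + 4 × 0.787 + 0.718)/6 = 0.791, against 0.789 simulated.
- No class difference: Φ(0) = 0.50 whatever the yield.

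**A second set of assumptions** (12 participants, two within-person classes, centroid-based linear classifier, same cross-validation) agrees in direction. Keeping 100/70/40/10% at random gives 0.660/0.660/0.660/0.658. Dropping the noisiest 0/20/40/60% gives 0.703/0.727/0.745/0.766. With no signal and nothing lost it gives 0.500.

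**The case against.** Several points on the other side stand and set the limits of this one.

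- Technical performance is a named focus of the endpoint, and balanced accuracy and F1 are ordinary measures of it. A reader might infer that the metrics are unrelated to the endpoint, or that they show nothing about the workflow. The documents do not support that: the metrics answer one of three parts, and any computed value shows that some data ran from end to end.
- The metrics are given as examples, so others are not excluded. But the category remains performance metrics, and the Discussion applies its reading to any of them.
- A reader might infer that lost data will go unreported. They will not go wholly unreported. Completeness of data collection is part of the primary endpoint (2.6.1) and is verified at each session (2.5). It is monitored during the home week (2.4), and missing data are described per outcome measure (2.7). Unrecorded trials should appear there. What none of these names is loss in synchronisation, segmentation or feature extraction.
- The Discussion sentence is also a safeguard, since it warns against generalising from twelve people. That half is right and should stay. Leave-one-subject-out testing is also a sound choice: the protocol justifies it by the dependence of cycles within a person and the risk of leakage.
- A reader might infer that a failing pipeline would be carried into the next trial. The protocol ties no progression rule to machine-learning accuracy, so that is speculation.
- Step-by-step yields are detail that an article may leave to the full protocol or analysis plan, and their absence alone would be no finding. The stated interpretation is different, because a plan that follows it would repeat the error.
- The simulation's results follow largely from its construction. They show that accuracy is not a yield measure and say nothing about how much loss to expect here.

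**Conclusion.** The point holds in limited form. For technical performance the named metrics are suitable. For data quality and workflow viability they are not, and the two statements that present them as evidence of pipeline feasibility (2.6.2 and the Discussion) are wrong for those parts. The gap is confined to loss inside the pipeline, after recording.

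On size: under the assumed data, accuracy is flat to within 0.002 when yield falls from 95% to 25% at random. It rises by 0.091 (0.827 − 0.736) when the noisiest cycles are the ones lost. These values depend on the assumed classes, noise and loss mechanism. The flat result under random loss and the chance result without signal do not depend on those details, provided that enough cycles remain to train the model. The rise depends on failed cycles being the harder ones to classify, which is plausible but not documented.

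Severity is minor: the endpoint is secondary and exploratory, and no decision rule rests on it.

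**What to change.** 1. In 2.6.2, make within-pipeline yield the main measure for the data-quality and viability parts: the share of recorded trials synchronised, the share of gait cycles segmented, the share with a complete feature vector, and the number of participants with usable data in each condition.
2. Keep balanced accuracy and F1 as a description of technical performance. Show beside them the number of cycles and participants they are computed on, and the chance level for the class mix. Drop the claim that they demonstrate pipeline feasibility.
3. In the Discussion, keep the caution that no machine-learning metric is a generalisable predictive result, and remove the statement that the metric indicates workflow feasibility. Refer to the yield measures for that.

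Cost: a few extra counts from the processing steps and changes of wording. No added visits, participants or measurements.
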